##### Effectiveness Study

Primary outcome data will be analyzed using a multilevel model (R, version 4.0+; package lme4) to investigate whether there is a significant difference between the level of professional care support moments (frequency or duration) per week in the baseline phase and the effect phase. The dependent continuous variable is the frequency and duration of professional care support moments per week. We will analyze all professional care support moments provided, as well as a selection of the specific professional care support moments connected to the goals for which the social robot is deployed.

The independent binary variable is the moment of measurement (baseline phase or effect phase). Because there are multiple measurements per participant at both phases, the model will contain a random intercept for participants. Time will be included in the model as a covariate. Measurements are consequently averaged and compared within participants per phase. Following the intention-to-treat principle, all participants will be included in the analysis, regardless of whether the participant has used the social robot in all weeks during the intervention adjustment phase and effect phase. Because multilevel models handle missing values well, no imputation is needed [34]. Quantitative secondary outcome data will be analyzed similarly. To assess the robustness of the primary outcome, additional per-protocol analyses and completers analyses will be performed as sensitivity analyses.

Clinical relevance will be determined per participant. Here, two conditions must be met as follows: (1) a Reliable Change Index of >1.96 for the level of support provided by care professionals [35] and (2) with CiSR, the participant progresses in carrying out the selected activities independently (GAS score of ≥+1 for at least one goal).

The follow-up data will be used to determine how many participants continue to receive CiSR, whether the effect is sustained in these participants, and what reasons there are to discontinue CiSR.

As recommended by recent single-case intervention research design standards [36], visual analysis will be conducted on the primary outcome. For each participant, data will be presented graphically to compare and interpret changes in patterns, level, and slope within and between different phases (baseline, intervention adjustment, effect, and follow-up). Using the contextual data collected for each case during the study period, we will qualitatively explore and report missing data patterns and discuss their implications for the robustness of the findings.

Qualitative data will be coded and analyzed thematically using Atlas.ti (version 8.4.20; Lumivero, LLC).

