**Effectiveness study**
RQ1: What is the effectiveness of compare care involving a social robot (CiSR) on the support provided by professional caregivers (frequency or duration) compared to care as usual (CAU)?RQ2: Does the potential effectiveness of CiSR persist at follow-up?RQ3: Which individual goals are set to be achieved by CiSR, and are these goals attained?RQ4: What is the effectiveness of CiSR on the well-being of individuals with challenges in daily structure and planning?RQ5: How does CiSR affect the work engagement of care professionals?

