#### Training of Care Professionals

To integrate the social robot into the care process, care professionals need to be trained through a demonstration and guided practice in using the technology. This will be carried out during a training session, in which an implementation expert will install the social robot together with the care professional or the care team. After this, the care professional will introduce the social robot to the participant. Besides learning how to use the technology, care professionals will need to change their working routines, as the social robot will handle reminders that they previously provided. Thus, they will need to deimplement CAU for these specific goals. This will be discussed with the care professionals during weekly phone calls.

The social robot will be integrated into the care process, with the research team monitoring its implementation by logging and resolving support requests related to Tessa. During weekly phone calls with the care professionals, a researcher will check whether they have encountered any prevailing problems and directly help to solve these problems (eg, technical problems, problems with programming the messages, and communication issues between the various parties involved).

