##### Analysis

###### Power

Due to the staggered design, power was determined through simulation using the R (R Foundation for Statistical Computing) packages simstudy and lme [33]. For a varying number of participants, 1000 datasets reflecting the staggered design were generated, all assuming a normally distributed outcome variable, a correlation between consecutive weeks of Pearson *r*=0.8, and a final effect of Cohen *d*=0.5 between the baseline phase and the first week of the effect phase (increasing linearly in 6 weeks). With 24 participants, a significant intervention effect (*P*<.05) was observed in 80.3% (803/1000) of cases, between the measurements from the baseline phase and those from the effect phase. Assuming 22% dropout (based on the study by van Dam et al [17]), the study is adequately powered when a total of 24 + (0.22 × 24) = 30 participants are included.

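### The primary endpoint is not fixed: the text wavers between frequency *or* duration and frequency *and* duration, leaves goal-linked support unranked, and powers one unspecified outcome

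*Protocol article*

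**What the plan says.** Five places in the protocol article bear on what the primary endpoint is.

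- **Primary Outcome.** One outcome is named, the support given to the participant per week. The diary records both how often support is given and how long it lasts. Neither is named as the endpoint.
- **RQ1 (Textbox 1).** The question concerns "support provided by professional caregivers (frequency or duration", that is, one metric or the other.
- **Effectiveness Study (analysis), first sentence.** The baseline-versus-effect comparison again uses *or*.
- **Same section, next sentence.** "The dependent continuous variable is the frequency and duration of professional care support moments per week". Two quantities are now called one dependent variable. A third sentence widens the scope: "We will analyze all professional care support moments provided, as well as a selection of the specific professional care support moments", the selection being the moments tied to the robot goals. No order is given.
- **Power.** The simulation has one normally distributed outcome, and "a significant intervention effect (*P*<.05) was observed in 80.3% (803/1000) of cases". It does not say which metric or scope that outcome stands for.

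Two further passages depend on the choice. The individual clinical-relevance rule applies a Reliable Change Index to the level of support, again with no metric. The Health Economic Evaluation expresses its effect as a reduced number of support moments, which is a frequency.

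**The concern.** The planned multilevel model takes one continuous response, and no composite of frequency and duration is defined. At least two models must therefore be fitted, and nothing says which one answers RQ1. The two can disagree: if the robot takes over many brief reminders, the count may fall while total minutes hardly change. Under *or*, whichever metric is favourable could be reported as the answer, at an error rate above the nominal 5%.

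The unranked goal-linked analysis adds to this. Under Training of Care Professionals, staff hand reminders over to the robot: "Thus, they will need to deimplement CAU for these specific goals". A fall in goal-linked support therefore partly reflects delivery of the intervention. It cannot by itself show that total support fell, which is the expected finding stated in the Discussion.

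The description of the study as adequately powered cannot be attached to a particular endpoint either.

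**Working it through.** **The plan's own figures.** 803/1000 = 80.3% with 24 participants. For dropout, 24 + 0.22 × 24 = 29.28, rounded up to 30, so the stated total reproduces. The 80.3% could not be reproduced. The inputs given are "a final effect of Cohen *d*=0.5 between the baseline phase and the first week of the effect phase" and "a correlation between consecutive weeks of Pearson *r*=0.8"; the correlation beyond adjacent weeks and the fitted simulation model are not stated. Simulations with a random-intercept model gave from 19.5% to about 100%, depending on those choices. The variants bracket 80.3%, so it is not called wrong, and it is used below only as an anchor.

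**Number of tests.**

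| Reading | Analyses that could answer RQ1 |
|---|---|
| One metric, total support | 1 |
| Either metric, total support; goal-linked supplementary | 2 |
| Either metric, total or goal-linked | 2 × 2 = 4 |

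**Familywise error.** Inputs: α = 0.05 from the Power section (two-sided assumed, since sidedness is not stated) and a common correlation ρ between test statistics. The article gives no ρ, so a range is shown.

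Independent tests: 1 − 0.95² = 9.75%; 1 − 0.95⁴ = 18.5%.

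Correlated tests, with c = 1.96 and k tests:

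FWER = 1 − ∫ [Φ((c − √ρ·u)/√(1−ρ)) − Φ((−c − √ρ·u)/√(1−ρ))]^k φ(u) du

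| ρ (assumed) | k = 2 | k = 4 |
|---|---|---|
| 0 | 9.75% | 18.5% |
| 0.5 | 9.1% | 15.6% |
| 0.7 | 8.4% | 13.0% |
| 0.8 | 7.8% | 11.4% |
| 0.9 | 7.0% | 9.4% |

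A simulation with 400,000 multivariate normal draws agrees to within about 0.1 percentage point (7.1% and 9.5% in the last row). Every entry exceeds 5%.

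**If *and* means that both metrics must succeed.** Type I error is then not inflated, but power is. With 80.3% for each metric, the power for both lies between 0.803² = 64.5% (independent) and 80.3% (perfectly correlated). So this reading does not match the single-outcome power calculation either, unless the two metrics move together exactly.

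**If the tests were kept co-equal with Bonferroni.** Anchor: 1.960 + 0.852 = 2.812, where 0.852 is the normal quantile of 0.803.

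- Two tests, α = 0.025: power Φ(2.812 − 2.241) = 72%. For 80.3%, n = 24 × ((2.241 + 0.852)/2.812)² ≈ 29 evaluable.
- Four tests, α = 0.0125: power Φ(2.812 − 2.498) = 62%. For 80.3%, n = 24 × ((2.498 + 0.852)/2.812)² = 34.1, so 35 evaluable, or 35 × 1.22 = 42.7, so 43 enrolled by the article's own inflation.

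Naming one endpoint keeps α at 0.05 and leaves 24 and 30 unchanged.

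**The case against.** The strongest reply is that the article does name one primary outcome, weekly support with no restriction to goals, which matches the analysis of all support moments. The goal-linked analysis is introduced as an addition and can fairly be read as a supplementary subset. Hierarchies and multiplicity rules are also commonly left to an analysis plan, which is not shown here. These points stand. They bring the milder reading down to two tests, and the absence of an alpha adjustment is not itself the finding. They do not remove the contradiction over the metric. Choosing the primary endpoint belongs in the protocol, and here the text says *or* twice and then *and*.

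A reader might infer more than the text supports:

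- **Four primary tests, with success claimed on any one.** No success rule is written, and the count of four is one reading only. The 18.5% also needs independence, which is not credible: goal-linked support is part of total support, and frequency and duration describe the same logged moments.
- **The goal-linked analysis is circular, or the result most likely to be positive.** The article gives nothing to rank the likely results. Changing staff routines is part of the intervention, and usual care has components beyond reminders, so a fall there need not show only that an instruction was followed.
- **A shift of support to other tasks would go unseen.** The all-support analysis captures net support, nonroutine support is described in the diary, and changes in content are asked about weekly. The clinical-relevance rule also requires progress on at least one goal.

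**Conclusion.** The point holds as an unfixed and self-contradictory primary endpoint. The metric is absent from the outcome definition and stated in two incompatible ways in RQ1 and the analysis. The goal-linked scope is unranked, and the power statement belongs to no identified outcome.

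If either metric of total support may answer RQ1, the familywise error is about 7% to 10%. If goal-linked versions also count, it is about 9.5% to 16%, with 18.5% as the independence ceiling. These figures rest on two-sided tests at 0.05, on assumed correlations (0.9 down to 0 for two tests, 0.9 to 0.5 for four), and on reading *or* as allowing either metric to suffice. An analysis plan or registration record that is not shown may already settle the choice. The published text would still need to be brought into line with it.

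**What to change.** Before analysis:

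1. Name one metric of total professional support per week, either frequency or minutes, as the single primary endpoint. Reconcile the choice with the Health Economic Evaluation, which counts support moments. If minutes are chosen, explain why the economic effect uses a different metric, or align the two.
2. Test the other metric of total support next, in a fixed sequence at 0.05, only if the primary test succeeds.
3. Label both goal-linked analyses secondary, because staff are asked to withdraw usual care for those goals.
4. Use the same wording in RQ1, Primary Outcome, Power and the Effectiveness Study analysis, and state which metric and scope the Reliable Change Index uses.

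The cost is wording in the protocol, analysis plan and registration. No new data or participants are needed, and the sample size stands. The article schedules analysis from the second quarter of 2025, so the decision should be dated; if it was made after outcome data were seen, the report should say so. The downside is that the non-primary metric and the goal-linked results can no longer carry the primary claim.

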### Study Design

A multiple baseline single case study will be conducted in everyday care practice. Multiple baseline single case studies are based on the principle that evidence of a causal effect can be strengthened by assigning participants to baselines of varying lengths. The staggered introduction of the intervention helps to rule out alternative explanations such as maturation or testing and session experience [20].

The study period consists of 3 phases (within 13 weeks) and a follow-up phase (Figure 1, Textbox 2, and Table 1). The number and timing of clusters is based on power calculations while considering the practical feasibility. The intervention does not allow for blinding within the trial.

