**Figure 1 figure1:**
[figure not shown]
Study planning overview. CAU: care as usual; CiSR: care involving a social robot.

Summary of the study period.Baseline phase: participants will be randomly allocated to 1 of 4 baseline lengths (2, 3, 4, and 5 weeks, respectively), resulting in 4 different clusters. In the baseline phase, participants will receive care as usual.Intervention adjustment phase: a 6-week phase in which each participant starts to receive compare care involving a social robot (CiSR), that is, using and adjusting to the social robot.Effect measurement phase: this period varies in length based on the cluster to which the participant is assigned, from 2 to 5 weeks. Participants will continue CiSR.Follow-up phase: to observe whether the results are maintained while participants continue CiSR, a follow-up measurement will take place 6 months after the start of the intervention adjustment phase.

**Table 1 table1:** Study planning.

Cluster	Baseline	Intervention	Effect	Follow-up	
1	2 weeks of CAU^a^	6 weeks of CiSR^b^	5 weeks of CiSR	Weeks 34-35	
2	3 weeks of CAU	6 weeks of CiSR	4 weeks of CiSR	Weeks 35-36	
3	4 weeks of CAU	6 weeks of CiSR	3 weeks of CiSR	Weeks 36-37	
4	5 weeks of CAU	6 weeks of CiSR	2 weeks of CiSR	Weeks 37-38	

^a^CAU: care as usual.

^b^CiSR: care involving a social robot.

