#### Start of the Study Period

Within each participating care organization, the research period for all locations will begin simultaneously.

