Single-case experimental designs (SCEDs) are increasingly used in behavioral research and provide a clear framework for establishing causal relationships between interventions and outcomes. SCEDs are particularly useful in applied settings and allow researchers to conduct a thorough examination of an individual’s response to an intervention in their daily setting [41]. While enabling analysis of data on a group level due to the multiple baseline design, the design of this study involves frequent measurements for each participant, providing valuable insights into individual effects as well. The use of 4 clusters enhances the internal validity by controlling for potential confounding variables [42]. Given the large variation in support needs regarding daily structure and planning (nature, frequency, and severity) between participants, SCED enables a personalized approach essential to investigating the effectiveness of CiSR [43]. Although personal goals are formulated for each participant, our multiple baseline SCED enables adequate comparison of results between individuals and the application of findings to daily care practice [44]. While the results of group studies may not always apply to individuals, especially in the field of long-term care, SCED focuses on studying how individuals respond to an intervention. This can help understand how to apply the same intervention in the care and support for people with similar conditions [45]. Therefore, with the use of SCED methodology —which allows for an in-depth analysis of individual responses and the identification of causal relationships— findings can be meaningfully interpreted beyond the specific setting [46]. When compared to randomized clinical trials, SCEDs are often questioned for their lack of generalizability. In this study, generalizability is increased by 30 systematic replications (the same intervention, ie, CiSR, with different participants’ characteristics and settings) [47]. This study takes place in a Dutch residential care context. However, given the use of SCED methodology, we anticipate that the findings will be transferable to individuals with similar challenges in residential care settings in other countries.

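### The baseline-versus-effect contrast leaves out the only study weeks in which usual care and robot care run side by side, so the staggered start does not separate study-week effects from the robot effect in the primary test

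*Protocol article*

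**What the plan says.** **Design.** The summary of the study period and Table 1 give four clusters: "participants will be randomly allocated to 1 of 4 baseline lengths (2, 3, 4, and 5 weeks, respectively), resulting in 4 different clusters". Next comes a common "Intervention adjustment phase: a 6-week phase in which each participant starts to receive compare care involving a social robot (CiSR"). Of the effect phase the summary says "this period varies in length based on the cluster to which the participant is assigned, from 2 to 5 weeks". Start of the Study Period adds: "Within each participating care organization, the research period for all locations will begin simultaneously".

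**Role given to the stagger.** Study Design: "The staggered introduction of the intervention helps to rule out alternative explanations such as maturation or testing and session experience". Strengths and Limitations: "The use of 4 clusters enhances the internal validity by controlling for potential confounding variables".

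**Primary test.** Analysis, Effectiveness Study: "The independent binary variable is the moment of measurement (baseline phase or effect phase". The model has a random intercept per participant and time as a covariate, whose form is not given. The Power section uses the same two-phase contrast and assumes an effect of d=0.5, "increasing linearly in 6 weeks".

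**Adjustment weeks.** Table 2 has the diary kept in every phase. In the analysis of the primary outcome, the adjustment weeks appear only in the visual analysis per participant.

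**The concern.** A multiple-baseline design gains its strength from weeks in which some participants have crossed over while others have not. Whatever else happens in such a week affects both groups, and the difference between them can be attributed to the intervention. If those weeks are not in the model, the test becomes a before-after comparison that relies on the time term to remove everything else.

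At stake is the reading of a positive primary result. A staffing change or a change in how diaries are kept, arriving between the last baseline week and the first effect week, would be reported as reduced support due to the robot. The protocol's causal wording would then claim a protection that the test does not have.

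**Working it through.** **1. Weeks by cluster (Table 1).**

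| Cluster | Baseline | Adjustment | Effect |
|---|---|---|---|
| 1 | 1-2 | 3-8 | 9-13 |
| 2 | 1-3 | 4-9 | 10-13 |
| 3 | 1-4 | 5-10 | 11-13 |
| 4 | 1-5 | 6-11 | 12-13 |

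Over all clusters, baseline occupies weeks 1-5 and effect weeks 9-13, with no overlap. Both conditions are present only in week 3 (robot: cluster 1), week 4 (clusters 1-2) and week 5 (clusters 1-3). In each of these the robot users are in adjustment weeks 1 to 3.

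**2. Planned data, time by week.** Ten study weeks remain (1-5 and 9-13). Columns: intercept 1 + phase 1 + week indicators 9 = 11. The phase column is the sum of the indicators for weeks 9-13, so the rank is 10 of 11 and the robot effect is not estimable.

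**3. Planned data, linear time.** On the retained rows, a step starting at week 6, 7, 8 or 9 is 0 in every baseline row and 1 in every effect row. It is identical to the phase column, so its coefficient is exactly 1.00 under any correlation structure. With no robot effect and a 0.3 SD drop from week 7, the model returns -0.30, which is 0.3/0.5 = 60% of the design effect. A straight-line drift contributes 0. A unit step inside the baseline or effect weeks (week 4 or 11) contributes -0.24 under AR(1) and -0.38 under exchangeable correlation, that is, in the opposite direction.

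**4. All 13 weeks.** Assumptions: 24 participants, 6 per cluster, SD 1, correlation 0.8 as AR(1) or exchangeable (the Power section does not say which), generalised least squares with the true covariance. Power = Φ(0.5/SE - 1.96) + Φ(-0.5/SE - 1.96), two-sided 5%. The ramp reaches its full value in the first effect week.

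| Model | Share of a week-7 step in the robot effect (exch. / AR(1)) | Power (exch. / AR(1)) |
|---|---|---|
| Planned weeks, linear time | 1.00 / 1.00 | 38% / 17% |
| All weeks, terms for weeks 1-6 since start, linear time | 0.73 / 0.92 | 41% / 17% |
| All weeks, ramp, linear time | 1.14 / 0.97 | 51% / 17% |
| All weeks, terms for weeks 1-6 since start, week effects | 0.00 / 0.00 | 29% / 10% |
| All weeks, ramp, week effects | 0.00 / 0.00 | 30% / 10% |

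The last two models have full rank: 1+1+6+12 = 20 columns and 1+1+12 = 14 columns. Their SEs are 0.36 and 0.35 (exchangeable), and 0.78 and 0.75 (AR(1)). Example: 0.5/0.35 - 1.96 = -0.53, and Φ(-0.53) = 0.30. If the ramp is instead complete in the sixth adjustment week, power with week effects is 39% and 12%.

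**5. The plan's own 80.3%.** This was not reproduced. A simulated random-intercept fit to AR(1) data gave 86.7% without a time term, with type I error about 30%. Generalised least squares without time gave 57.6% under AR(1) and about 100% under exchangeable correlation. With linear time the results are the 17% and 38% above. The correlation form and time term used in the plan's simulation are not described, so this does not show the figure to be wrong, and the present point does not depend on it.

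**The case against.** Several objections have force, and they set the limits of the point.

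- **Time is in the model.** A reader might infer that any change between weeks 5 and 9 is counted as a robot effect. That is too strong. If time is linear, a constant drift is removed, and some non-linear patterns bias the estimate the other way. What is counted in full is a step in the gap.
- **Not all six adjustment weeks matter equally.** One might say that the plan discards six weeks of concurrent comparison. Only study weeks 3-5 have both conditions, that is, the first one to three adjustment weeks of clusters 1-3.
- **The wording is measured.** The protocol says that the stagger helps and enhances. It does not say that it settles the matter. The visual analysis covers all phases and the discussion relies on combining it with the statistics. This stands, but graphs per participant are not the test.
- **Omitting a running-in phase is a legitimate choice.** It targets the settled effect, which is what was powered. This is a fair reason to keep the contrast, but it does not give the contrast a concurrent comparison.
- **Starts may differ between organizations.** A common start is stated only within an organization. Different start dates with time coded by calendar date could create some overlap. The article states neither.
- **The unbiased analysis is weak.** This is true and must be disclosed. It argues for modest causal claims and does not strengthen the planned test.

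**Conclusion.** The point holds in this bounded form. On Table 1's weeks, the primary contrast contains no study week with both conditions. With linear time, a common step at study weeks 6-9 enters the robot estimate at 100%; with time by week, the estimate does not exist. The statistical test therefore does not deliver the protection against maturation, testing effects and confounders that Study Design and Strengths and Limitations attach to the stagger.

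These two results follow from the layout and need no assumption about correlation or sample size. They assume that time is coded by study week. The power and SE figures rest on 6 participants per cluster, correlation 0.8 and the assumed 6-week ramp.

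The documents do not support going further and calling the primary result uninterpretable or the stated power wrong. Nor does adding the adjustment weeks by itself cure the problem: with linear time kept, 73-114% of a week-7 step still leaks in.

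**What to change.** 1. Pre-specify an analysis of all 13 diary weeks with study week as a factor, a random intercept per participant, and one of two robot codings: separate terms for weeks 1-6 since robot start plus an effect-phase term, or the linear 6-week ramp that the Power section already assumes.
2. Report it beside the primary contrast, and state the form of the time term in the primary model.
3. Limit the causal wording in Study Design and Strengths and Limitations to what this analysis supports.
4. State its imprecision in advance. The 95% half-width at 24 participants is about 1.96 × 0.35 = 0.69 SD to 1.96 × 0.36 = 0.71 SD under exchangeable correlation, and 1.96 × 0.75 = 1.47 SD to 1.96 × 0.78 = 1.53 SD under AR(1). The analysis may well be inconclusive.

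The cost is analysis work and wording only, since the diaries are already kept in every phase. The ramp coding assumes the shape of the effect. The free coding avoids that assumption but adds parameters.

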**Methods:**

We will assess the effectiveness of social robot care in reducing the level of support provided by care professionals in a multiple-baseline single case study. In total, 30 participants will be randomly allocated to 1 of 4 clusters, determining the baseline length (2, 3, 4, or 5 weeks) of a 13-week study period, and a 2-week follow-up will be conducted 6 months after participants start using the robot. During baseline, participants will receive care as usual. After baseline, participants will use the robot as part of their care plan. For each participant, 3 to 5 personal goals will be formulated, and attainment of these goals will be evaluated weekly. A health economic evaluation from a societal perspective will be performed to assess the cost-effectiveness.

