#### Randomization

The researcher ([name]) will randomly assign each location within the participating care organizations to a cluster. Due to practical considerations, randomization will be applied at the location level rather than the participant level, as this ensures a consistent and manageable implementation for the care team. This cluster determines the duration of the baseline length (2, 3, 4, or 5 weeks). The first 4 locations will be randomly assigned to one of the 4 clusters using a random sequence generator. Subsequent locations will be assigned to the cluster with the fewest participants at that moment. If multiple clusters have the same number of participants, a random sequence generator will be used to decide the assignment. The risk of unequal exposure to external influences is limited due to the initial randomization of the first 4 locations and the balanced allocation strategy of the following locations, which aims to maintain the balance between the clusters.

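### The primary model leaves out the randomised location and any decay of correlation across weeks, so its standard errors may be too small and the 5% level is not assured

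*Protocol article*

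**What the plan says.** All sections are in the protocol article.

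- **Unit of allocation.** The Randomization section states that "randomization will be applied at the location level rather than the participant level". The Abstract says "In total, 30 participants will be randomly allocated to 1 of 4 clusters", and the study-period summary (Textbox 2) also speaks of participants. In the article a cluster is a baseline-length group, not a location.
- **Model.** Under Effectiveness Study (analysis): "Primary outcome data will be analyzed using a multilevel model (R, version 4.0+; package lme4"). Its only random effect is given with its reason: "Because there are multiple measurements per participant at both phases, the model will contain a random intercept for participants". The contrast is within participant: "The independent binary variable is the moment of measurement (baseline phase or effect phase"). Then: "Time will be included in the model as a covariate".
- **Averaging.** The next sentence reads: "Measurements are consequently averaged and compared within participants per phase". It is unclear whether weekly values or one mean per phase enter the test.
- **Power.** The simulation assumes "a correlation between consecutive weeks of Pearson" *r*=0.8 and *d*=0.5, and reports 80.3% power with 24 participants. It does not say whether the correlation falls with lag, and it mentions no location.

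**The concern.** Residents of one location share a care team. That team keeps the support diary, is trained in the robot and drops its old routines together, so residents' changes from baseline may be alike. A participant intercept does not capture this. Separately, a random-intercept model in lme4 takes residuals as independent, which makes any two weeks of one person equally correlated. If the true correlation fades with lag, the model counts more independent information than there is. Both faults tend to give intervals that are too narrow and too many false positives in the test on which the effectiveness claim rests.

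**Working it through.** **Inputs from the article.** 24 participants; baseline of 2, 3, 4 or 5 weeks, 6 adjustment weeks, then 5, 4, 3 or 2 effect weeks (Table 1), so 7 analysed weeks each; *r*=0.8; *d*=0.5; P<.05.

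**Assumptions.** SD 1, 6 participants per baseline length, linear week, two-sided test, no dropout. The number of locations and the likeness of residents within a location are not given, so both are varied.

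**1. The plan's own figure.** Power of 80.3% is not reproduced for the described contrast. A random intercept with linear time gives 38% if the correlation is equal at all lags and 19% under AR(1). This does not prove the figure wrong, because the simulation's correlation structure and fitted model are not fully described.

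**2. Serial correlation, no location effect, no true effect, time in the model.**

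| True correlation | Rejections at nominal 5% |
|---|---|
| 0.8 at all lags | 4.8% |
| AR(1), 0.8 | 7% to 8% over repeated simulations |
| Stable part 0.5 plus decaying part (lag-1 value still 0.8) | 9.9% |

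Under AR(1) the model's standard error is about 7% too small. Paired phase means hold 4.6% to 4.7% in all three cases.

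**3. What location does.** Let location *k* add a constant c to every week and a shift g to the effect phase only. A participant's change contains (c + g) − c = g. The constant cancels; the shift does not. Simulation agrees: adding a constant location effect gives 5.0% to 5.2% (equal lags) and 7.0% to 7.9% (AR(1)), in line with step 2.

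**4. Shared change, time in the model.**
- Location-by-phase variance 0.06 to 0.30, 4 to 8 locations: about 4% to 10%.
- Location-by-week variation carrying 5% to 20% of the variance, 4 to 12 locations: 5.5% to 15.9% (equal lags) and 7.9% to 20.2% (AR(1)).

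**5. Shared change, phase means compared.** With v the variance of one participant's change, τ² the location-by-phase variance and m residents per location:

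ICC = τ²/(τ² + v); DE = 1 + (m − 1) × ICC; error ≈ 2Φ(−1.96/√DE).

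- *v, equal lags:* 0.2 × (1/2 + 1/5) = 0.140 and 0.2 × (1/3 + 1/4) = 0.117; mean 0.128.
- *v, AR(1), 2 and 5 weeks:* 0.900 + 0.724 − 2 × 0.127 = 1.37. For 3 and 4 weeks: 0.831 + 0.774 − 2 × 0.126 = 1.35. Mean 1.36.
- *Low end* (AR(1), τ² = 0.06, 8 locations, m = 24/8 = 3): ICC = 0.06/1.42 = 0.042; DE = 1.08; error 6%.
- *High end* (equal lags, τ² = 0.30, 4 locations, m = 6): ICC = 0.30/0.428 = 0.70; DE = 4.5; error 36%. The sample variance is also too low, by the factor 1 − 5 × 0.70/23 = 0.85. Then 4.5/0.85 = 5.3 and the error is about 39%.

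Simulation over the same settings gives 6% to 41%. The top of the range is a strong assumption: √0.30 = 0.55 SD, more than the planned effect of 0.5.

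**6. After modelling the true within-participant correlation** (no location effect): error returns to 4.5% to 5.3%. Power for *d*=0.5 with linear time is 38% (equal lags) or 16% (AR(1)).

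**The case against.** The strongest defence is that every participant receives both forms of care and the contrast is within participant. Location fixes only the baseline length, so the usual penalty for a cluster-randomised parallel comparison does not carry over. That stands for constant location effects. It does not cover shared change.

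It is also fair that a correlation of 0.8 between neighbouring weeks does not contradict a random intercept. If it is equal at all lags, the planned model is right on this point. If phase means are analysed, the serial part disappears, though the location part remains.

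The full analysis plan is not shown and could add terms. This defence is partial: the article names the random structure and justifies it by repeated measurements alone.

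A reader might infer four stronger things that the documents do not support:

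- *That the 5% level is definitely broken.* This depends on lag decay, the number of locations and the location correlation, none of which is stated.
- *That the error is several times nominal from serial correlation alone.* That arises only if time is left out, and the plan includes it.
- *That differing individual responses inflate the error.* With time in the model and person-level SDs of 0.25 to 0.5, simulation gave 3% to 4% (equal lags) and 6% to 7% (AR(1)), so this adds nothing.
- *That the causal claim fails.* That claim rests on the staggered start. A misstated standard error affects precision, not the source of identification.

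**Conclusion.** The point holds in conditional form. The stated primary analysis leaves out the unit that was randomised and does not provide for decaying correlation, so the nominal 5% is not assured. From serial correlation alone the departure is nil to modest. Location-level change could make it larger, most of all if phase means are compared with few locations, but every location figure rests on assumed inputs and is a range, not an estimate. Shared change is plausible because teams log the outcome and alter their routines together. The allocation wording in the Abstract and Textbox 2 contradicts the Randomization section whichever model is used.

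**What to change.** 1. Bring the randomised unit into the analysis: a location-by-phase or location-by-time random effect, small-sample cluster-robust standard errors by location, or a location-level randomisation test. A location intercept by itself does not suffice.
2. Allow serial correlation across weeks, for example AR(1) in nlme or glmmTMB, with small-sample degrees of freedom.
3. State whether weekly values or phase means are analysed.
4. Re-run the power simulation with that model, giving the assumed lag structure, number of locations and location correlation, and restate the figure.
5. Correct the Abstract and Textbox 2 to say that locations are allocated.

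**Cost.** Plan wording and a different model call; each participant's location is already known from the allocation. The change should be fixed before results are seen. Intervals will be wider, restated power may be well below 80.3%, and the location variance will be imprecise if locations are few. A randomisation test must follow the actual procedure, in which only the first four locations and later ties are random. Four locations allow 4! = 24 assignments, so the smallest attainable P value would be 1/24 = 0.042.
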